##### SES-sensitive implementation strategy

The SES-sensitive implementation strategy will encompass all the topics described in the regular implementation strategy, but will be tailored to match the needs of the lower-SES target group.

The GP nurses will receive a 3-h training (instead of a 2-h training), and follow-up meeting of 1.5 h (approximately 2 months after the training visit) in which extra elements of the SES-sensitive implementation strategy will be addressed. This additional section of the training was developed in collaboration with a representative of the Dutch Centre of Expertise on Health Disparities (Pharos). An important component is the recognition and guidance of lower-SES patients who might benefit from the online CDMIs. GP nurses will be taught about the concept and consequences of health-literacy skills and ways to recognise and align with the needs of patients with a lower SES or low/limited health-literacy skills. They will practice with methods to provide support to patients with lower SES or health-literacy skills (e.g. easier language and communication, teach-back method). They will also be strongly advised to provide a more directive approach to guiding patients and encouraging them to use the CDMIs. Practical tips will be given to do this, such as: not immediately offering the online CDMIs during the first visit, but after trust and alliance have been established, seeking contact more often (face-to-face, by telephone or monitoring system) to provide guidance, helping patients create an account, indicating which exercises the patient should do (an overview of exercises and suggestions is given in the manual), doing the online exercises with patients during face-to-face sessions before doing them alone (modelling), focussing on one or a few exercises to reduce the chance of experiencing failure, using appropriate language and checking whether information is understood (e.g. using the teach-back method).

The GP nurses in this condition will also have access to a helpdesk service, at least two implementation team meetings and ongoing communication activities from the research teams, but special attention will be paid to the lower-SES target group in all these actions.

Additional elements of the SES-sensitive implementation strategy aimed at the patients are:
▪ Extra guidance from the GP nurse, when needed, during the registration process (creating an account, username/password, intake questionnaire, etc.)▪ Extra guidance from the GP nurse, if necessary, with the exercises (e.g. the GP nurse and the patient practice the exercise together during a consultation)▪ A more proactive approach of delivering support by the GP nurse (e.g. extra reminders, extra contact moments by email or phone)

### Outcome measures

#### Primary outcome

The (difference in the) participation rate of patients with a lower SES in the CDMIs is the primary outcome. Participation is defined as participating in at least one face-to-face session with a GP nurse (as registered by the GP nurse) and engaging with at least two exercises in the online CDMIs (as determined with the user data of the online CDMIs). It is hypothesised that in the SES-sensitive implementation strategy arm of the trial the participation rate of lower-SES patients will be significantly higher than in the regular implementation strategy arm. This outcome requires an operational definition of SES, but SES can be defined in various ways. Indicators that are commonly used are education, income and work status/occupation [31–35]. Education is a widely used indicator, especially in the Netherlands, and has some advantages over the other two indicators [36–38]. First, the level of education is generally stable after early adulthood, whereas work status and level of income fluctuate more. Second, in general, respondents are willing to report their level of education, while respondents might be unwilling to disclose or even misstate the level of their income [38, 39]. For these reasons, education will be the main indicator of lower SES in this study. In addition to education level, income, work status and status level of the neighbourhood will be taken into account because these indicators cover different dimensions of SES and are, although interrelated, not interchangeable with education [33, 34].

Therefore, in this study, a lower SES will be defined as:
The highest completed educational level is intermediate vocational education (i.e. between lower and higher vocational education, in Dutch: MBO in Dutch: MBO) or lower, and/orThe respondent is unemployed (looking for work) and lives in a neighbourhood with a negative status level score, and/or:The total gross family income of the respondent is below the social minimum income in the Netherlands (per July 2017), and lives in a neighbourhood with a negative status score

Self-reported education will be assessed with a single item (What is your highest completed educational level?) with eight response options: none/primary school, lower vocational education, intermediate secondary education, higher secondary education, intermediate vocational education, higher vocational education, academic education, and other type of education. We use the term ‘lower SES’ in this study as we include intermediate levels of education in our definition of lower SES. In the Netherlands, four levels of intermediate vocational education are discerned. Persons who report an intermediate vocational education as their highest completed education level will be asked to indicate which type of intermediate vocational education they completed (answer options correspond to the four levels). Generally, the first level is used as the cut-off for highest completed educational level in a low-SES definition (e.g. by Statistics Netherlands). However, we use the fourth level as the cut-off for highest completed educational level. We chose a higher cut-off point because it is mainly the highly educated (i.e. higher vocational education and academic education) that are currently reached with e-health interventions, despite the risk of depression generally increasing as educational level decreases [8].

Self-reported gross family income will be assessed with a single item. In the Netherlands, the social minimum income is dependent upon living arrangements (persons who live alone or as a single parent: rounded to an average of €1100 for this study, and for persons with any other type of living arrangement: €1550) which is reflected in the answer options: more or less than €1100 or more or less than €1550. Self-reported work status will be assessed with a single item using the following answer options: employed/self-employed, unemployed, occupationally disabled, student, volunteer work, retired, homemaker. Status level scores of the neighbourhood will be assessed by asking respondents their four-digit zip code. The Netherlands Institute for Social Research provides status scores for every zip code. For this study, the status level scores of 2016 will be used. A negative status level score indicates a lower than the Dutch average status level score of the years 1998–2016.

### Secondary outcomes

#### Psychological complaints

In line with the previous study on the effectiveness of the self-guided online CDMIs, we assessed the complaints targeted by the CDMIs and additional psychological outcomes as secondary outcomes.
▪ Depressive complaints will be measured using the 8-item Patient Health Questionnaire (PHQ-8) [40]. Items can be scored from 0 (not at all bothered) to 3 (bothered nearly every day) which results in a total score ranging from 0 to 24. Higher scores correspond to higher levels of depressive complaints. Sum scores of 5, 10, 15 and 20 represent cut-off points for mild, moderate, moderately severe and severe depression, respectively▪ Sleep problems will be measured with the Jenkins Sleep Evaluation Questionnaire (JSEQ) [41]. It consists of four items that are scored on a 6-point scale (0 = not at all, 5 = 22–31 days) and can be added to obtain a total score ranging from 0 to 20. Higher scores indicate more sleep problems▪ Stress will be measured with the 10-item Perceived Stress Scale (PSS-10) [42]. Items are scored on a 4-point scale (0 = never, 4 = very often), resulting in a total score ranging from 0 to 40. Higher score indicate higher levels of stress▪ Worry will be assessed using the 11-item Penn State Worry Questionnaire (PSWQ) [43]. Items can be scored from 0 (not at all typical of me) to 5 (very typical of me) which results in a total score ranging from 11 to 55. Higher scores correspond to higher levels of worry▪ Anxiety will be measured with the Generalised Anxiety Disorder Scale (GAD-7) [44]. The seven items are rated on a 4-point scale (0 = not at all sure, 4 = nearly every day). Items are summed which results in a total score (range 0–28), with higher scores defining a higher level of anxiety severity▪ Well-being will assessed with the 5-item World Health Organisation Well-Being Index (WHO-5) [45]. The items can be scored from 0 (at no time) to 5 (all of the time) which results in a total score ranging from 0 to 25. Higher scores correspond to higher levels of well-being

#### Implementation-related factors

##### Health literacy

To increase the uptake of self-management interventions among people with a lower SES it may be important to take their health-literacy skills into account. Health-literacy skills, defined by the WHO as ‘the cognitive and social skills which determine the *motivation* and *ability* of individuals *to gain access to, understand and use information* in ways to promote and maintain good health’, play a crucial part in empowering people to use self-management interventions [23, 46]. Low or limited health-literacy skills are more prevalent among vulnerable groups, including people with a low education and a low income [22, 47, 48]. Examples of ways to pay attention to health-literacy skills in the implementation of interventions are: increasing the skills of health care providers to recognise low health-literacy skills, adapting communication into an easier understandable way, and helping people navigate through an intervention [49].

Health literacy will be assessed using the 14-item Dutch Functional Communicative and Critical Health Literacy Scale (FCCHL) [50, 51]. The items are scored on a 4-point scale (1 = never to 4 = always). Items can be summed and divided by the total number of items to obtain a total score ranging from 1 to 4, with higher scores indicating higher levels of health literacy.

##### Satisfaction and feasibility

Patients in both implementation groups will be asked about the usefulness and satisfaction with the intervention (e.g. ease of use, effectiveness in reducing/handling complaints, relevance of exercises, and other content, overall satisfaction) at the 3- and 12-month follow-ups. They will also be asked about the usefulness and satisfaction with the guidance they were provided with at the 3-month follow-up. In addition, in-depth interviews (*n* = 10) will be conducted to illicit patient experiences with the intervention, their preferences for the delivery of the online CDMIs in primary care and factors that they deem relevant for the sustained (successful) implementation of the intervention.

GP nurses will be asked about their experiences and satisfaction with the online intervention and guiding patients in using the intervention. They will be asked to rate the implementation materials (including the monitoring system and manual), their overall opinion of the intervention, which strategies they used to guide patients (with a high and lower SES), and how competent they felt in guiding patients with a lower-SES level. Based on the Unified Theory of Acceptance and Use of Technology (UTAUT model) [52]. GP nurses were asked to rate statements (1 = totally agree, 5 = totally disagree) relating to five dimensions that may directly or indirectly impact the use of technology according to the model: performance expectancy (four items), effort expectancy (four items), social influence (four items), facilitating conditions (four items) and behavioural intention to use the intervention (seven items). Moreover, statements relating to GP nurse attitudes (four items) and self-efficacy (two items) with respect to (their ability in) using the intervention will be included. Like patients, GP nurses will also be invited to participate in in-depth interviews (*n* = 10) to gain insight into their experiences with implementing the intervention in their daily practice, providing guidance, and facilitators and barriers for (further) implementation.

##### Fidelity and adherence

Adherence to the intervention by patients will be assessed with user data that are collected in the online CDMI system (i.e. the number of number of completed exercises and diary/monitor entries). The fidelity of the GP nurse to the intervention will be assessed by questioning GP nurses in the follow-up questionnaires about the guidance that they have given (e.g. the rate to which they recommended exercises, the type of exercises recommended, the intensity of the guidance). Furthermore, GP nurses will be asked to report per patient about the number of face-to-face consultations. These data will also be used to provide some insight into the costs of the intervention. For costing we shall make use of the pertinent Dutch guideline for economic evaluation and rely on the standard cost prices reported therein. These will be indexed to the study’s reference year 2017. The user data of the monitoring system will be used to evaluate the use of this tool by GP nurses.

#### Additional factors

##### Sociodemographic factors

In addition to income, work status and neighbourhood status (see above), other sociodemographic factors that will be assessed are: age, gender (male/female), living arrangement (alone, with partner, with partner and children, without partner and with children, with parents, other), marital status (single, married, civil partnership, divorced, widowed) and country of birth.

Data will be assessed in all patients, not only lower-SES patients. First, secondary outcomes (such as impact on complaints and well-being) will primarily be examined for within-group differences, but we are also interested in between-group differences. Second, because ‘low SES’ and ‘participation’ can be defined in various ways we will conduct additional analyses for which data from all patients are needed. Lastly, in order to compare outcomes with other studies, secondary outcomes of all patients must be assessed.

### Sample size calculation

The sample size is based on the main outcome, namely participation rate of patients with a lower SES. This is defined as participating in at least one face-to-face session with a GP nurse and completing two exercises in the online CDMIs (see above). We expect a (base) participation rate of 18% with the regular implementation strategy. Due to a paucity of studies about online psychological interventions offered and guided by primary care professionals, this percentage is based on previous (baseline) participation rates of lower-educated people in studies of online self-help interventions for depression [18, 20]. This percentage also takes into account that our definition of participation entails more than just starting with the intervention/trial and that attrition in e-health can be related to indicators of lower SES [9]. We aim to double the participation rate of lower-SES patients to 36% by using the SES-sensitive implementation strategy; a smaller effect was not deemed to be relevant. As far as we know, there is no empirical evidence that might support this doubling; however, our rationale is that with specific training and specific materials this percentage of participating lower-SES patients can be reached. The difference between these fractions (0.18 vs. 0.36) will be tested at a two-sided significance level of 5% and a power of 80%. Accounting for the clustering in the data with six patients on average per GP nurse (range 2–14 patients) and an intraclass correlation of 0.02, we need *n* = 114 patients in each condition (in 19 GP nurses per condition) or 228 participants in total. This normative sample size calculation was performed in Stata version 14.2 statistical software package using the clustersampsi-procedure, taking into account the mean cluster size, cluster size variation and the intraclass correlation [53]. The intraclass correlation value of 0.02 was based on the Hospital Anxiety and Depression Scale (HADS)-depression scores in the primary care setting as reported by Adams and colleagues (2004), Table 5 [54].

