**Methods/design:**

The online ‘Complaint Directed Mini-Interventions’ (CDMIs) for stress, sleep and worry complaints, which were found to be (cost-)effective in a self-guided format, will be implemented in the primary care setting using a blended care format (i.e. combining e-health with face-to-face sessions) with minimal guidance provided by the GP nurse. The main aim is to evaluate whether a SES-sensitive implementation strategy improves the participation rate (i.e. reach) of lower-SES patients in the blended online CDMIs as compared to a regular implementation strategy in a cluster randomised controlled trial. Randomisation will occur at the level of the GP nurse, and 228 patients will be included in the study. The primary outcome is the participation rate (completing at least one face-to-face session and two online exercises) of the lower-SES target group. It is hypothesised that this percentage will be higher in the SES-sensitive group as compared to the regular group. Secondary objectives are to evaluate the implementation process, to monitor and evaluate psychological complaints (depression, sleep, stress, worry and anxiety) and well-being over time. Patient assessments will take place at baseline, 3 and 12 months post baseline.

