In the present study, the online ‘Complaint Directed Mini-Interventions’ (CDMIs), which were found to be (cost-)effective in a self-guided format [17, 18], will be implemented in the primary care setting using a blended care format (i.e. combining the e-health intervention with supporting face-to-face sessions that will be provided by the GP nurse). The online CDMIs are short, low-threshold unguided web-based interventions that target depressive complaints by focussing on highly prevalent complaints that are demonstrably associated with depression and have a substantial economic impact: stress, sleep problems and worry [19]. There are three different CDMIs: ‘Sleep better’, ‘Stress less’ and ‘Worry less’, and each CDMI contains various modules and exercises (see [18] for more information). A feature of the CDMI intervention framework is that patients can choose the complaints that they want to focus on (by choosing the CDMIs that they want to use), and it also allows patients to choose the modules and exercises that they want to do and in what order (pick and mix). The CDMIs are based on cognitive-behavioural techniques as well as elements from solution-focussed therapy, mindfulness and positive psychology. They were developed to be as easy to understand and use as possible. They are focussed on ‘doing’ rather than ‘reading’ with the aim to appeal to a broad range of people, including those with a lower educational level. However, in line with other studies of e-health interventions for depression [9, 20], mainly individuals with a high education level or income participated in the randomised controlled trial (RCT) of the self-guided format (more than 70%). This indicates that there is a clear need for implementation strategies that increase the reach of e-health interventions for depression, including the CDMIs, particularly among lower-SES groups. They may particularly benefit from a more proactive strategy [21], including more proactive and intensive guidance, and additional strategies that take the specific needs of this target group into consideration such as low(er) health-literacy skills [22, 23]. Therefore, a SES-sensitive implementation strategy will be developed in collaboration with primary care professionals and patients, and will be compared to a regular implementation strategy in a randomised controlled trial.

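### The 228 is derived for a comparison among lower-SES patients but is also the total enrolment of a trial open to every SES, so on that outcome 80% power needs about 90% or more of those enrolled to be lower-SES

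*Protocol article*

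**What the plan says.** The Sample size calculation opens by naming the outcome: "The sample size is based on the main outcome, namely participation rate of patients with a lower SES". Its inputs are "We expect a (base) participation rate of 18% with the regular implementation strategy" and "We aim to double the participation rate of lower-SES patients to 36% by using the SES-sensitive implementation strategy", tested two-sided at 5% with 80% power. It assumes six patients on average per GP nurse (range 2 to 14) and an intraclass correlation of 0.02. The result is 114 "patients in each condition (in 19 GP nurses per condition) or 228 participants in total". The Primary outcome section and the Abstract likewise define the outcome as the participation rate of lower-SES patients.

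On who is enrolled, the Abstract says: "Randomisation will occur at the level of the GP nurse, and 228 patients will be included in the study". The patient eligibility list covers age, complaint, internet access, Dutch language, acute comorbidity and consent; SES is not on it. The section on sociodemographic factors adds: "Data will be assessed in all patients, not only lower-SES patients". It justifies this by the secondary and additional analyses.

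Two places point another way. The Aim words its goal as a percentage of lower-SES participants. The Additional analyses section plans sensitivity analyses that treat lower SES as the outcome.

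**The concern.** If the primary outcome is a rate among lower-SES patients, the 114 per arm must all be lower-SES patients. The Abstract uses the same total for all patients included, and patients of every SES can join. Both statements hold only if nearly everyone enrolled is lower-SES. The article gives no expected share, no inflation for the remainder and no lower-SES recruitment target.

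What is at stake is the stated power of the primary test. The protocol says that an effect smaller than a doubling would not be relevant. If power for that doubling were 70% or 56%, the trial would miss it 30% or 44% of the time, and a null result would say little.

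**Working it through.** **Inputs.** From the Sample size calculation: p1 = 0.18, p2 = 0.36, two-sided 5%, power 80%, mean cluster size m = 6 (range 2 to 14), ICC 0.02, 19 GP nurses and 114 patients per arm. The coefficient of variation (CV) of cluster size is not printed. I take CV = 0 (equal clusters) and CV = 0.5 (range divided by 4 is 12/4 = 3; 3/6 = 0.5).

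**Step 1: reproduce 228.**

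- Individual randomisation, with mean proportion 0.27: n = [1.96 × √(2 × 0.27 × 0.73) + 0.842 × √(0.18 × 0.82 + 0.36 × 0.64)]² / 0.18² = [1.96 × 0.628 + 0.842 × 0.615]² / 0.0324 = 94.3, so 95 per arm.
- Design effect DE = 1 + ((1 + CV²) × m − 1) × ICC. This is 1.10 at CV 0 and 1.13 at CV 0.5.
- 95 × 1.10 = 104.5 and 95 × 1.13 = 107.3, so 18 clusters of six, or 108 per arm.
- With t quantiles on 2(k − 1) degrees of freedom for k clusters per arm, the pooled-variance formula gives 109.6 (CV 0) and 112.6 (CV 0.5). Both need 19 clusters, that is 114 per arm and 228 in total.

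The printed figure therefore reproduces as the number of patients in the analysed denominator.

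**Step 2: power if 228 of every SES are enrolled and only a share s is lower-SES.** The analysed number per arm is 114s and the mean cluster size is 6s. The effective number is n_eff = 114s / DE, with DE computed at m = 6s. Power = Φ[(0.18 × √n_eff − 1.96 × 0.628) / 0.615].

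Example at s = 0.7 and CV 0.5: 114 × 0.7 = 79.8; m = 4.2; DE = 1 + (1.25 × 4.2 − 1) × 0.02 = 1.085; n_eff = 73.55; power = Φ(0.509) = 69.5%.

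| Lower-SES share (assumed) | Lower-SES patients per arm | Power, CV 0 | Power, CV 0.5 | Enrolment needed for 228 lower-SES (228/s) |
|---|---|---|---|---|
| 100% | 114 | 83.6% | 82.6% | 228 |
| 90% | 102.6 | 80.0% | 79.0% | 254 |
| 80% | 91.2 | 75.6% | 74.7% | 285 |
| 70% | 79.8 | 70.3% | 69.5% | 326 |
| 50% | 57 | 56.6% | 56.0% | 456 |

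Power reaches 80% at a share of about 90% (CV 0) to 92.5% (CV 0.5). Under the t-based versions the results are a little lower, for example 67 to 69% at a share of 70%, and the break-even share rises to as much as about 98%.

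**Step 3: power if all enrolled patients are in the denominator.** With 114 per arm the result is the first row of the table: 82.6 to 83.6%, so nothing is lost.

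**Step 4: the ICC, a secondary check.** The plan states: "The intraclass correlation value of 0.02 was based on the Hospital Anxiety and Depression Scale (HADS)-depression scores in the primary care setting". With all 114 per arm lower-SES and CV 0.5, an ICC of 0.05 gives DE = 1 + (7.5 − 1) × 0.05 = 1.325, n_eff = 86.0 and power 76%. The 0.05 is my assumption; the protocol gives no ICC for participation.

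**The case against.** The strongest reply is that the text does not settle the denominator. The wording of the Aim can mean a share, and a sensitivity analysis with lower SES as its outcome only makes sense if higher-SES patients are counted too. On that reading all 228 contribute and the stated power holds. This stands, and it is why a loss of power cannot be asserted outright. It does not rescue the document, because the Abstract, the Primary outcome section and the Sample size calculation then describe a different outcome.

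A second reply is that the Sample size calculation, read alone, could mean 228 lower-SES patients, with the Abstract merely abbreviating. That is also possible. The power would then be as stated, but the Abstract would understate enrolment whenever any higher-SES patient joins.

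A third is that no passage gives the lower-SES share. The definition is broad: it reaches the fourth level of intermediate vocational education and adds routes through unemployment and income. The share could therefore be high. The Background reports more than 70% with high education or income in the previous self-guided trial, but that trial had a different setting and used a different classification. It is a hint that the share may be low, and no forecast.

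Finally, the ICC and its source are openly disclosed. Borrowing it is a weakness to probe and does not make the calculation wrong.

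**Conclusion.** The inconsistency is real and should be corrected. One number serves both as the lower-SES sample that the primary comparison needs and as the total enrolment of a trial open to every SES. On the outcome as the Abstract, the Primary outcome section and the Sample size calculation define it, the 80% is not delivered unless roughly 90% or more of those enrolled are lower-SES. Power is about 79 to 80% at a 90% share, 75% at 80%, 70% at 70% and 56% at 50%, given the protocol's rates and ICC and the assumed CV of 0 to 0.5.

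A reader might infer that the trial is certainly underpowered, or that 228 was miscalculated. The documents support neither inference. The arithmetic reproduces. The all-patient reading, or a reading of 228 as lower-SES patients, keeps power at about 83%. The size of any loss depends on a share that is not stated. What does hold is that every reading leaves at least one section in need of correction.

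**What to change.** 1. State one primary denominator, either lower-SES patients or all patients, and make the Abstract, Aim, Primary outcome, Sample size calculation and Additional analyses agree with it.
2. Say whether 228 counts lower-SES patients or all patients.
3. If it counts all patients and the denominator is lower-SES, replace the 80% with the power and the detectable difference at the projected lower-SES share, and state that share.
4. As a secondary addition, show power at a higher ICC such as 0.05 beside 0.02, because the 0.02 does not come from participation data.

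The cost is rewording and, under item 3, a less favourable stated power; no extra patients are needed. If the sponsor instead chooses to recruit until 228 lower-SES patients are reached, total enrolment rises to 228 divided by the share, for example 326 at 70% or 456 at 50%.
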